**Methods/design:**

We will conduct a cluster randomized controlled trial in 40 villages in Liuyang, Hunan Province, China, home to approximately 400 patients with schizophrenia. Half of the villages will be randomized into the treatment group (village doctor, or VD model) wherein village doctors who have received training in a schizophrenia case management protocol will manage case records, supervise drug taking, educate patients and families on schizophrenia and its treatment, and monitor patients for signs of relapse in order to arrange prompt referral. The other 20 villages will be assigned to the control group (case as usual, or CAU model) wherein patients will be visited by psychiatrists every two months and receive free antipsychotic medications under an on-going government program, Project 686. These control patients will receive no other management or follow up from health workers. A baseline survey will be conducted before the intervention to gather data on patient’s socio-economic status, drug compliance history, and clinical and health outcome measures. Data will be re-collected 6 and 12 months into the intervention. A difference-in-difference regression model will be used to detect the program effect on drug compliance and other outcome measures. A cost-effectiveness analysis will also be conducted to compare the value of the VD model to that of the CAU group.

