### Drug compliance

Since chlorpromazine was introduced in 1952, antipsychotics have become the principal element of schizophrenia treatment, and compliance is key to reducing relapse. A number of studies outside of China have demonstrated that partial compliance with antipsychotic medication is a common problem and is associated with greater risk of hospitalization [7,8]. In a German study, ‘Needing someone to remind them to take their medication’ contributed to partial compliance in 62% of patients [9]. In a previous unpublished study conducted by our group, only 20.8% of villagers with schizophrenia in Liuyang Municipality were under any kind of supervision of their drug-taking, and less than 50% of schizophrenia patients took their daily medication over the past month, consistent with the results of a study in Qingpu, a municipality near Shanghai, which showed that 60% of patients fail to comply with prescribed treatments [10].

### Project 686

The ‘Management of Major Psychoses Treatment Project,’ funded by the central government and known as Project 686, aims to improve the treatment of severe psychoses by dispensing free medications in rural China, with psychiatric professionals visiting rural communities every two months to dispense antipsychotics to patients. Based on our preliminary data, among the 4,000 Project 686 patients registered in Liuyang Municipality, Hunan Province, as having severe mental disorders -- most of them schizophrenia patients -- only approximately 70% obtained their free antipsychotics in the previous two months, and for those who got medications, no information exists regarding actual use. Despite the availability of free medication, challenges to compliance persist; these include engaging family members in compliance, and the two-month interval between psychiatric visits and dispensation of medications [11].

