### Procedures

Following a pilot study (see Section below), 40 villages (excluding the pilot study villages) will be randomly selected in Liuyang Municipality. We will conduct a baseline survey of patients with schizophrenia in the villages, collecting data on social demographics, compliance rates, clinical characteristics, and outcome measures. Researchers will explain the research to participants and obtain written informed consent from both patients and family member. And after the randomization, VDs and family members of patients will receive training and education in the 12-month case management protocol as noted in Section above. Researchers will visit VDs every month during the first three months of the study and every three months thereafter for the remaining nine months of the study, obtaining feedback and giving follow-up instructions, and recording and monitoring VDs’ case management work via questionnaire.

In the CAU model, control villages will continue to receive bimonthly visits by psychiatric professionals, who will dispense free antipsychotics per existing Project 686 protocol. No other interventions will be introduced.

Follow-up interviews will be conducted with patients in both VD and CAU model villages at 6 months and 12 months into the intervention, collecting the same data as that collected at baseline (see below).

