### Instruments

Four types of statistics will be collected at baseline and at 6 months and 12 months into the study:

Socio-demographic characteristics: age, sex, education level, marital status, work, economic status, domestic situation (living alone, with family, or with friends).

Clinical characteristics: years of illness, number of bed days in psychiatric hospital in previous two years.

Compliance: This is our primary dependent variable measure. The binary variable Drug Compliance (DC) will be recorded by interviewing patients and their family members. We define as ‘compliant’ patients who, over the past month, have taken all pills as prescribed; otherwise, patients are recorded as ‘non-compliant.’ We will report 1-month, 3-month, 6-month and 12-month compliance as the proportion of patients achieving compliance over the total number of patients. In addition, a continuous variable Drug Compliance Score (DCS) will be used to measure medication compliance. The DCS score will be measured by dividing the actual number of pills taken by the total number of pills prescribed multiplied by 10 over a given period of time, with scores ranging from 0 (complete non-compliance) to 10 (complete compliance). For example, if a patient over the past month took 20 pills out of 100 prescribed, his compliance will be (20/100) × 10 = 2 for the past month.

Clinical/outcome measures: Four types of measures will be collected.

Symptoms score: Schizophrenia is often described in terms of positive and negative (or deficit) symptoms. Negative symptoms respond less well to medication [20], particularly to the antipsychotics that are typically used for cases in our research. Therefore, we will concentrate on the positive symptoms as these correlate more strongly with medication compliance. The Brief Psychiatric Rating Scale (BPRS) will be used to evaluate positive symptoms. The BPRS is an 18-item rating scale that has been widely used in psychiatric practice and research in China, and has good to excellent reliability and validity.

Social functions: We will use the global assessment of functioning (GAF) scale, in which a score of 0 to100 is converted to a disability weight ([100-GAF score]/100). Patients with a disability weight of 0.40 or greater are classified as moderately to severely disabled.

Quality of life score: We will use the QALY weights developed by Lenert *et al*. [21].

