In the above equation, β_1_ indicates program effect, *i.e*., the effectiveness of village doctors in managing villagers with schizophrenia as measured by the average change in DCS for those in the treatment group (VD) minus the average change in DCS for those in the control group (CAU).

There are several advantages to using this model. First, the coefficient in which we are most interested, β_1_, is more efficient than other estimators as it has a smaller variance or standard error than a simple difference estimator when unobserved determinants of DCS persist over time for a given individual. Second, this model eliminates possible pre-program differences in DCS between the treatment and control groups; for example, while using cluster randomization, we may not achieve true randomization at the individual level since it is possible (though unlikely) that all eligible individuals within a cluster could be assigned to a treatment or to a control group. Finally, the difference-in-difference equation allows for additional variables to be added to the treatment variable in the VD group. As these added regressors are possible determinants of the dependent variable DCS, including them improves the efficiency of the OLS estimator, β_1,_ which is the coefficient for program effect, thus addressing: potential bias introduced by imperfect randomization; partial compliance wherein patients with more severe illness in the VD group may at times elect not to comply with village doctors’ care, while patients with milder disease or more supportive family members in the CAU group may, of their own initiative, seek care from their village doctors; and attrition as severely ill patients are lost to follow-up (depending on the data collected, we will seek instrumental variables to address bias introduced by drop-outs). That said, we anticipate a high take-up rate by patients in rural Liuyang because the free antipsychotics program has been operating in the municipality for several years and has been well accepted by patients and their families. Given past experience in Liuyang, we anticipate a drop-out rate of 10% over the course of the study.

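### The added regressors do not deal with two-way cross-over, as the plan says they do, and no described item records village-doctor contact in control villages

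*Protocol article*

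**What the plan says.** All references are to the protocol article.

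- **Cross-over foreseen.** Under the comparison of the VD and CAU models, the authors allow for departures in both arms. On the intervention side, "patients with more severe illness in the VD group may at times elect not to comply with village doctors’ care". On the control side the departure foreseen runs the other way: "patients with milder disease or more supportive family members in the CAU group may, of their own initiative, seek care from their village doctors".
- **Claimed remedy.** The same paragraph says the extra regressors make β1 more efficient, and presents this as dealing with imperfect randomisation, this two-way partial compliance, and attrition. Instrumental variables are mentioned in connection with drop-outs alone.
- **The model.** The change in DCS is regressed on an arm indicator, socio-demographic variables, illness severity and family care.
- **Records of village-doctor work.** Case files and weekly medication records are among the services of the VD model (Intervention section). Under Procedures, "Researchers will visit VDs every month during the first three months of the study", then less often, with a questionnaire on the village doctors' case-management work.
- **Data from both arms.** "Four types of statistics will be collected at baseline and at 6 months and 12 months into the study". The items named are socio-demographic, clinical, compliance and outcome measures.
- **Expected uptake.** The authors write "we anticipate a high take-up rate by patients in rural Liuyang"; their reason is that the free-drug scheme is long established locally and well received.

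**The concern.** Covariate adjustment and handling of cross-over are different tasks. Baseline covariates explain variation in the outcome and can shrink the standard error of β1. They carry no information on whether a given patient received village-doctor care, so they cannot undo dilution of the contrast between arms. A reader who takes the statement at face value would treat β1 as already corrected for partial compliance and read it as the effect of receiving the care.

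The second half of the concern is practical. If the trial shows a small difference, the investigators will want to know whether the model of care did little or whether the arms ended up receiving similar care. That needs exposure measured alike in both arms, and the article describes such records for one arm only.

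**Working it through.** **Step 1: what β1 estimates.** Let δ be the effect of the care on those who receive it (taken as constant), c the share of CAU patients who obtain it and d the share of VD patients who do not. By assigned arm, the expected contrast is

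(1 − d)δ − cδ = (1 − c − d)δ.

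The only treatment term in the model is the arm indicator, so this is what β1 targets. Neither c nor d enters the equation. Baseline covariates that randomisation balances in expectation change the precision of β1 and leave the factor (1 − c − d) in place.

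**Step 2: where village-doctor care is recorded.**

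| Source in the article | VD villages | CAU villages |
|---|---|---|
| Case files | yes | not described |
| Weekly medication records | yes | not described |
| Researcher questionnaire on case management | yes | not described |
| Interviews at baseline, 6 and 12 months | no contact item named | no contact item named |
| Village-doctor time in the cost analysis | counted; source and arms not stated | source and arms not stated |

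Declined care in the VD arm is therefore at least partly recoverable. Care sought in the CAU arm has no described source.

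**Step 3: the plan's own sample size.** Inputs: DC 0.5 v 0.7, two-sided 0.05, 80% power, ICC 0.1, 10 patients per village (Sample size sections and Table 1).

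n per arm = [1.96√(2 × 0.6 × 0.4) + 0.842√(0.5 × 0.5 + 0.7 × 0.3)]² / 0.2² = 93

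Design effect = 1 + (10 − 1) × 0.1 = 1.9, and 93 × 1.9 / 10 = 17.7, so 18 villages per arm: 36 villages and 360 patients. Then 360 / 0.9 = 400. This reproduces the plan's figures. There is no separate allowance for cross-over.

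**Step 4: illustration of dilution.** The documents give no rates, so c and d are assumptions. I also assume that a CAU patient who crosses gains the full 20 points and a VD patient who declines gains none. With 180 analysed per arm, the effective number is 180 / 1.9 = 94.7 with the plan's design effect, or 180 / 1.8 = 100 if 9 patients per village remain (1 + 8 × 0.1 = 1.8).

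Power = Φ{[(p₂ − p₁)√n − 1.96√(2p̄(1 − p̄))] / √(p₁(1 − p₁) + p₂(1 − p₂))}

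For 10% in each arm, p₁ = 0.5 + 0.1 × 0.2 = 0.52 and p₂ = 0.7 − 0.1 × 0.2 = 0.68. With n = 94.7 the argument is (1.557 − 1.358) / 0.684 = 0.29, which gives 61.5%.

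| c = d | Proportions | Contrast | Power, n = 94.7 | Power, n = 100 |
|---|---|---|---|---|
| 0% | 0.50 v 0.70 | 20 points | 80.7% | 82.8% |
| 5% | 0.51 v 0.69 | 18 points | 71.9% | 74.2% |
| 10% | 0.52 v 0.68 | 16 points | 61.5% | 63.8% |
| 15% | 0.53 v 0.67 | 14 points | 50.3% | 52.4% |

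The illustration uses binary DC because the article states no standard deviation for DCS.

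**The case against.** Several objections have force.

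- **Silence in a condensed article.** A reader might infer that cross-over cannot be measured at all. The article does not support that. Its list of instruments is not exhaustive: the family-care regressor and village-doctor time are both used and neither is named there. Both arms are interviewed, a contact item may sit in a questionnaire not shown, and a societal cost comparison might well require one. This stands, and it limits the measurement point to what the article describes.
- **Foreseen, not expected.** The text says patients may cross over, and it anticipates high take-up. It does not predict a rate.
- **The power figures may overstate the loss.** The 0.7 in Table 1 is the proportion in the treatment group, so it may already allow for some non-uptake. The 0.5 comes from Project 686 patients in Liuyang, where ordinary contact with village doctors may already be included. CAU village doctors have no study training and do not hold the drugs, so a CAU patient who sees one is unlikely to gain the full effect. This stands; the figures are an illustration.
- **Two apparent contradictions are weak.** The abstract says "These control patients will receive no other management or follow up from health workers", which describes what the control arm is given; patients who seek care themselves do not contradict it. Under Project 686, "only approximately 70% obtained their free antipsychotics in the previous two months", but that concerns drug collection among all registrants with severe mental disorders. It does not measure uptake of village-doctor care, and the anticipated high take-up carries no figure to conflict with.
- **A small result remains interpretable.** β1 is a valid effect of assignment whether or not patients cross over. A reader might conclude that a null result would be unreadable; what would be lost is only the explanation for it.

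None of this rescues the statement that the regressors address partial compliance. That statement is printed in the article, and a fuller document could not make it true.

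**Conclusion.** The concern holds in a limited form. The error that is certain is the claim of method: the plan credits covariate adjustment with handling two-way cross-over, while its model has no term for care received and β1 stays at (1 − c − d)δ. The gap in measurement is narrower. Described records of village-doctor care exist for the VD arm only, and nothing described captures contact in CAU villages. Whether the full questionnaire does so cannot be told from the article.

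The size is unknown because no cross-over rate is given. Under the assumptions of full gain or loss for those who cross, 10% in each arm would take the contrast from 20 to 16 points and power from about 81–83% to about 62–64%. Smaller effects in those who cross, or a 0.7 that already includes non-takers, would make the loss smaller. This should be corrected, but it does not threaten the validity of the as-randomised comparison.

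**What to change.** 1. Withdraw the statement that the added regressors address partial compliance. Describe β1 as the effect of assignment to the VD model, and keep it as the main result.
2. At the existing 6- and 12-month interviews, ask patients and families in both arms (a) how many contacts with the village doctor for schizophrenia they have had since the last interview, and (b) whether the village doctor handed out or watched medication in the past month. Report both by arm. If the full questionnaire already holds such items, say so.
3. If an effect of care received is wanted, use village allocation as the instrument in one secondary analysis, with the treatment defined as the whole VD package. Village-doctor contact alone would not serve, because allocation also brings family coaching, a second route to compliance that would breach the exclusion restriction.

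The cost is two more interview questions and, if chosen, one secondary analysis. No new visits are needed. The article reports the trial as still in its pilot phase, so on that account the interviews could still be changed.

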### Sample size

To minimize contamination and simplify project management, we will use one-stage clustered sampling. For a two-sided significance level of 0.05 and power of 80%, the sample size is calculated for both the binary variable Drug Compliance (DC) and the continuous variable Drug Compliance Score (DCS), with DC referring to a patient outcome achieving pre-defined compliance or not, while DCS refers to a score anywhere from 0 (no compliance) to 10 (full compliance), calculated as the proportion of the number of drugs actually taken by an individual divided by the number of drugs prescribed for that individual over a given period of time. As our previous study of Project 686 patients with schizophrenia in Liuyang Municipality showed a 50% compliance rate, or DC of 0.5, our calculations were based on the need to detect DC in the range of 0.5 (the current rate) to 0.7 (our hypothesized improvement). In conducting our sample size analysis, we used software developed by the University of Aberdeen, U.K., specifically for clustered randomized trials [19].

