### Sample size with the binary variable drug compliance (DC)

For a cluster randomized trial, the sample size must be ‘inflated’ over that of an individual randomized controlled trial (IRCT), taking into consideration the size of the cluster as well as the intra-cluster correlation coefficient (ICC). As we are uncertain about the ICC and the effect size associated with our intervention, we did a further sensitivity analysis (as shown in Table 1) on the minimum effect size detectable in relation to various sample sizes and ICCs, assuming a 5% significance level and 80% power.

**Table 1 T1:** Sample size with binary DC

**Proportion of patients achieving DC in the control group****	**Proportion of patients achieving DC in the treatment group**	**ICC**	**Number of clusters needed***
0.5	0.6	0.01	86
		0.05	114
		0.1	148
0.5	0.7	0.01	22
		0.05	28
		0.1	36
0.5	0.8	0.01	10
		0.05	12
		0.1	16

*The exercise uses a 5% significance level at a power of 80%, with 10 patients per cluster as suggested by Project 686 registries.

**The control group proportion of patient achieving DC is based on our current research in Liuyang.

From the table above, we can see that in order to detect a minimum increase in the proportion of patients achieving DC from 0.5 to 0.6, we will need a sample of at least 860 patients, even assuming a liberal ICC of 0.01. However, if we can achieve a minimum increase of 0.5 to 0.7, even at a conservative ICC of 0.1, only 360 patients are needed for this increase to be detectable. Assuming a patient drop-out rate of 10%, we arrive at a sample size of 400 patients. Project 686 records indicate that villages in the cluster have an average of 10 patients per village; consequently, 40 villages will be needed to gather a sample of 400 villagers with schizophrenia.

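### As written, the compliance model uses only patients with a final score, and neither the added regressors nor unnamed instruments can be relied on to remove drop-out bias

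*Protocol article*

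**What the plan says.** All places are in the protocol article.

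- **Outcome and visits.** Under Instruments, compliance is the primary dependent measure, as binary Drug Compliance (DC) and as the 0 to 10 DCS. The abstract gives the follow-up schedule: "Data will be re-collected 6 and 12 months into the intervention".
- **Model.** Comparison between VD model and CAU model lists t, chi-square and regression tests, then writes out one effect model, with DCS as the example. It is OLS with one row per patient. The dependent variable is DCS at the end of the study minus DCS at the start. The regressors are treatment and socio-demographic, severity and family-care variables. The text singles out the treatment coefficient as the quantity of main interest. Repeated-measures analysis is named only for symptoms and social function.
- **Expected problems.** The same section foresees "attrition as severely ill patients are lost to follow-up". It also foresees "partial compliance wherein patients with more severe illness in the VD group may at times elect not to comply with village doctors’ care", and CAU patients who seek village-doctor care on their own initiative. Drop-out is put at 10%.
- **Stated remedy.** The added regressors are said to make the estimator more efficient and, as a consequence, to deal with imperfect randomization, partial compliance and attrition. For drop-out alone, a further step is given: "depending on the data collected, we will seek instrumental variables to address bias introduced by drop-outs".

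**The concern.** There are three linked problems.

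1. A patient with no final DCS has no change score and cannot enter the equation as written. The 6-month DCS has no place in it either, so a decline recorded at 6 months in a patient who later leaves is not used.
2. The argument runs from efficiency to bias. A smaller standard error says nothing about whether the patients who remain represent those randomized.
3. The remaining remedy for drop-out is an instrument that is not named and is to be looked for in the light of the data. A valid one must affect drop-out without affecting compliance by any other route, which the data cannot verify. The estimate could then depend on which instrument is chosen.

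What is at stake is the validity of the compliance effect rather than its power, as the check shows.

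**Working it through.** **1. The plan's own sample size.** The inputs, from Sample size and Table 1, are two-sided 5% significance, 80% power, DC 0.5 versus 0.7, ICC 0.1, and a cluster size stated as "with 10 patients per cluster as suggested by Project 686 registries".

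- Per arm, individually randomized: (1.960·√(2·0.6·0.4) + 0.842·√(0.5·0.5 + 0.7·0.3))² / 0.2² = (1.358 + 0.571)² / 0.04 = 93.
- Design effect: 1 + 9·0.1 = 1.9. Then 93·1.9 = 176.7 per arm, so 18 villages per arm and 36 in all.
- This agrees with the text: "even at a conservative ICC of 0.1, only 360 patients are needed for this increase to be detectable". Then 360/0.9 = 400.

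The sample size reproduces and is not in dispute.

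**2. What 10% drop-out does to power.** Take 9 completers in each of 40 villages, which is 180 per arm. The design effect is 1 + 8·0.1 = 1.8, so the effective number is 180/1.8 = 100 per arm.

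- DC 0.5 versus 0.7: power 82.8%.
- DCS, 1 point: the plan's 38 villages give 190/1.9 = 100 effective per arm, the same number, so power stays at 80%.

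Power is therefore not the problem.

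**3. What drop-out can do to the DCS estimate.** Let p be the proportion lost in an arm, and s the amount by which the mean *change* in drop-outs falls short of that in completers. The mean change in all patients of an arm is the completers' mean minus p·s. Hence

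bias of the completers' difference = p(VD)·s(VD) − p(CAU)·s(CAU).

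The plan gives only the overall 10%. The split by arm and s are assumptions, and covariate adjustment is left out.

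| Loss VD / CAU | s VD / CAU | Bias (points) |
|---|---|---|
| 10% / 10% | 2 / 2 | 0 |
| 15% / 5% | 2 / 2 | 0.10·2 = 0.2 |
| 15% / 5% | 3 / 3 | 0.10·3 = 0.3 |
| 5% / 15% | 2 / 2 | −0.2 |
| 10% / 10% | 2 / 0 | 0.10·2 = 0.2 |

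A positive value overstates the VD effect. The target difference is 1 point (sample size section for DCS).

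**4. The same question for DC.** With completer rates of 0.7 and 0.5 and 10% missing in each arm, the difference in all patients can lie anywhere between

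- 0.9·0.7 − (0.9·0.5 + 0.1) = 0.08, and
- (0.9·0.7 + 0.1) − 0.9·0.5 = 0.28.

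If every drop-out is non-compliant it is 0.9·0.2 = 0.18.

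**5. What the regressors can do.** In a completers' regression they remove attrition bias only if, given arm and those regressors, drop-out is unrelated to the change in DCS. The severity variables listed are years since diagnosis and hospital days in the two years before the programme. Neither can reflect deterioration during the trial. For partial compliance, regressors do not undo non-uptake in VD villages or crossover in CAU villages. Analysis by allocated village simply includes such patients as randomized.

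**The case against.** The strongest reply is that the article does not say what a critical reader may take from it. Much of this stands.

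- **A primary model that discards drop-outs.** A reader might infer a declared primary complete-case analysis. No model is labelled primary, the equation is called an example, and no complete-case rule is stated. Loss of patients without a final DCS follows from the definition of the outcome. The absence of an imputation plan is no fault in an article.
- **The 6-month data are ignored.** They are not. Instruments promises to report 6-month compliance; only this model leaves the value out. The gain from using it also depends on when patients leave, which is not given.
- **Instruments for everything.** The instruments are tied to drop-out only. Partial compliance is left to regressors, and these are open-ended but not said to be chosen after seeing results. Nor can one say that no suitable instrument is collected, only that none is named.
- **A bias of 30% of the target.** A reader might support a 3-point shortfall from the plan's figures: half the patients fully compliant and a mean of 7 put the rest at (7 − 0.5·10)/0.5 = 4, a gap of 6. That is a gap in *level*, and a change score cancels a stable level gap. The 2 to 3 points used above are a pure assumption about change.
- **Severity is in the model, and analysts are blinded to group.** Both help in part. Severity adjustment works only under the condition in step 5. Blinding limits steering towards one arm, but it does not make an instrument valid.

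What the reply does not answer is the stated inference from efficiency to bias, or the stated data-dependent choice of instruments. Both are in the text, and neither is a detail left to an analysis plan.

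**Conclusion.** The concern holds in a limited form. The one effect model written out for compliance can use only patients with a final DCS and does not use the 6-month DCS, while the plan itself predicts severity-related loss. The claim that efficiency-improving regressors thereby deal with partial compliance and attrition is wrong. The fallback for drop-out is unnamed and depends on the data.

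The size is unknown. It is zero with equal loss and equal shortfall in change in the two arms. Under an assumed 15% versus 5% loss and a shortfall in change of 2 to 3 points, it is 0.2 to 0.3 of the 1-point target, with the sign set by which arm loses more. The documents do not support saying that the estimate will be biased, or by how much. They show only that the stated method offers no reliable protection if it is.

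**What to change.** - Analyse DCS at 6 and 12 months in a likelihood-based mixed model with village and patient effects, arm by visit, baseline DCS and a pre-specified set of baseline severity variables.
- State that all patients are analysed by their village's allocation, whatever care they took up.
- Pre-specify a delta-shifted sensitivity analysis for drop-outs, for instance by multiple imputation with drop-outs' values moved down by a range of amounts, separately by arm. This also covers patients lost before 6 months, who have no follow-up value for the model to use.
- Delete the claim that added regressors address partial compliance and attrition.
- Name any instrument in advance, with the reason why it should be valid, or drop it.

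The cost is revised wording and modest extra programming. The visits needed are already scheduled, so there is no new data collection. The mixed model relies on drop-out being missing at random given the observed data. That cannot be verified, and the sensitivity analysis is there to probe it.
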